**Fig. 2 Fig2:**
[figure not shown]
Design and scheduled appointments, assessments and interventions of the DECIDE-2 study

In the first and the last DeCM consultation appointment (T1 and T2), participants in both study arms will answer relevant study questions containing the pre-post assessment of primary and secondary endpoints, as well as the assessment of DeCM (not part of the study, see Material section). The last DeCM consultation (T2) will be scheduled six months after T1 ($$\pm$$ 30 days). Participating proxies in the treatment arm will answer additional questions included in T1 (as $$\text {T1}_{Treatment}$$) concerning treatment preferences of the PwD. If an advance directive is present for participating PwD in the treatment arm at T2, their proxies will complete additional study questions in T2 concerning the PwD’s treatment preferences ($$\text {T2}_{Treatment}$$). In both of these cases, the participating PwD will be absent during this query, as this could influence the ACD process and relevant endpoints.

Between T1 and T2, participants in the treatment arm will complete two supported ACD appointments. The time window between baseline assessment (T1) and the first ACD appointment (ACD1) will be 1-30 days, and the time window between the two ACD appointments (ACD1 and ACD2) will be 1-15 days. In the first appointment (ACD1), participants will complete the value anamnesis as the first part of supported ACD with their proxy present. If required, it is possible to split the completion of the value anamnesis into several appointments to reduce stress for PwD. In the second ACD appointment (ACD2), participants in the treatment arm and their proxy will finalize the process of supported ACD, deciding on their preferred form of advance health care planning and receiving support in its implementation. If they choose an advance directive or a guardianship directive, the dementia care manager will assist in drafting the document. If they opt for a power of attorney, they will be advised to consult a notary or counselling centre for PwD. If they decide against any form of advance directive, this decision will be documented. In the case of a decision to create an advance directive, a standardized assessment of participants’ capacity to consent will be conducted. A document with the participants’ decision regarding their own advance healthcare planning will be handed over to individual participants and their proxies for further use.

Importantly, between T1 and T2, participants from both study arms will be able to receive routine care, i.e., attend, if needed, further home-based DeCM consultations offered by the dementia care managers. We suspect that the alleviating effects of the intervention on proxy burden may emerge increasingly in the long term. Therefore, for all participants who provide consent, follow-up assessments of proxy burden will be conducted after the end of the main study period over a period of five years using a longitudinal design (T3-T7). Participants who agree will be contacted annually via mail or email to complete the follow-up survey.

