### Material

An overview of the instruments used for all measured variables is shown in Table 1. In addition to the existence of various advance health care documents (yes/no), the validity of an advance directive will be assessed, which is indicated by the existence of informed consent at the time the advance directive was created. For this purpose, a self-report questionnaire in accordance with the criteria for informed consent (adequate information, capacity to consent, voluntariness [17]) will be used.

**Table 1 Tab1:** Overview of collected constructs and applied instruments

Measured variable	Instrument	Time	Target individual
Primary endpoints			
Presence and validity of advance care documents	closed questions based on DECIDE-I study [9], usage of advance directive	T1, T2, T3-T7	PwD and proxy
Proxy burden	Zarit Burden Interview (7 items, [18–21]), Burden Scale for Family Caregivers (BSFC-s, 10 items, [22]).	T1, T2, T3-T7	proxy
Secondary endpoints			
Patient autonomy	Decisional Autonomy Scale (DAS, [23]), Perceived Autonomy in Old Age scale (WAA, [24, 25])	T1, T2	PwD
Patient-proxy congruence with treatment preferences	two items with different versions for PwD and proxy, Statement of Treatment Preferences^a^ [26]	$$\text {T1}_{Treatment}$$+$$\text {T2}_{Treatment}$$(proxy), ACD2 (PwD)	PwD and proxy separately
Decisional Conflict	Decisional Conflict Scale (16 items, [27])	T1, T2	PwD
Moderators, Mediators, confounding variables			
Demographic variables	diagnosis, age, gender, education, employment, living situation	T1, T3-T7	PwD
Health-related preferences	health literacy (single item, see [28]), need for autonomy (single item, see [29]	T1	PwD
Health-related variables	single screening item & checklist based on Mini-DIPS (Short Structured Clinical Interview for diagnosing Mental Disorders) [30]	T1	PwD
Depression	Geriatric Depression Scale [31]	T1	PwD
Cognitive status	Mini Mental Status Test [32]	T1	PwD
Advance Care Decision-Making^a^			
Value anamnesis	According to [11]	ACD1	PwD
Capacity to consent	CAT-AD [33]	ACD2	PwD
Advance care documents	Template by Bavarian State Ministry	ACD2	PwD and proxy

T1-T7 are illustrated in detail in Fig. 2

^a^Only for participants in treatment arm who create an advance directive

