### Outcome measures

The primary and secondary endpoints were chosen based on DeCM [39, 40] and advance care planning trials [4, 5]. The primary endpoints are the prevalence and validity of advance healthcare planning documents (advance directives or others) and proxy burden at pre- vs. post-measurement. Secondary endpoints are decisional conflict, patient autonomy, and patient-proxy congruence in preference. Details about the measurement of endpoints are provided in Material section.

Furthermore, the following demographic and clinical variables will be recorded: age, gender, education level, psychiatric comorbidities, health literacy, and the need for autonomy in medical decision-making. Although only age has previously been shown to be associated with the primary endpoints [41], the additional variables will be collected to provide a comprehensive description of the study population and to enable exploratory analyses.

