### Statistical methods

#### Required sample size and power analysis

The use of advance directives remains insufficiently widespread in Germany. Based on a German sample of 4,185 individuals between 50 and 90 years [42] and previous research with the target population [41], we anticipate a baseline prevalence of approximately 50% in our study population. Furthermore, the validity of existing advance directives is questionable in about 50% of cases [43]. The planned intervention will be considered practically relevant if this frequency increases by at least about 20-30 percentage points. Sample size calculations and simulations using the R package mixedpower showed that about 150 participants will be necessary to detect effects in the moderate range with sufficient power ($$> .8$$) in the focal effect of interest: i.e. the condition-by- time interaction in the (generalized) linear mixed-effects models (described in Statistical analyses section) both regarding our primary and secondary endpoints (see Outcome measures section).

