#### Statistical analyses

Assessment of the prevalence and validity of advance directives will be based on Bayesian generalized linear mixed-effects models. Bayesian estimation is more appropriate than maximum likelihood for smaller sample sizes, when the priors are chosen carefully [44]. We will use probit models modeling the change in the probability of the presence and validity of advance directives over time given the experimental condition and possible covariates (see Outcome measures section).

Outcome variables in these models are a) the binary variable for presence of an advance directive (yes/no), and b) the binary variable for the validity of the advance directive in the sense that it was both voluntarily given and based on informed consent (yes/no). In these models, the condition-by-time interaction and the contrast (whether the pre-post change in the ACD + DeCM condition is more pronounced than in the DeCM condition) are of primary interest. Likewise, analyses of proxy burden and of secondary endpoints will be based on Bayesian linear mixed effects models. Scale scores based on 5-point Likert scale items usually justify the use of ‘normal’ linear mixed effects models. If this is not feasible, the outcomes will be modeled as (ordered) categorical. To avoid loss of sample size, and consequently loss of statistical power, missing data in all model variables will be multiply imputed where appropriate (see Exploratory statistical solution development for missing data and small sample sizes section).

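### On the only schedule given, patient-proxy congruence has no control-arm assessment, which conflicts with the two-arm analysis and power stated for secondary endpoints

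*Protocol article*

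**What the plan says.** **Status.** Outcome measures: "Secondary endpoints are decisional conflict, patient autonomy, and patient-proxy congruence in preference".

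**Instruments.** Table 1 gives, in one row, "two items with different versions for PwD and proxy, Statement of Treatment Preferences". Footnote a, which limits collection to treatment-arm participants who create an advance directive, is attached to the Statement only. The Material text likewise describes the two items as answered by proxy and person with dementia, with no mention of arm, and then adds the Statement for the restricted group.

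**Timing.** That row has a single Time cell: T1_Treatment and T2_Treatment for the proxy and ACD2 for the person with dementia (it ends "proxy), ACD2 (PwD"). The other two secondary endpoints are timed at plain T1 and T2.

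**Definition of those occasions** (Data collection):
- T1_Treatment: "Participating proxies in the treatment arm will answer additional questions included in T1".
- T2_Treatment: "If an advance directive is present for participating PwD in the treatment arm at T2, their proxies will complete additional study questions in T2".
- ACD2: "Between T1 and T2, participants in the treatment arm will complete two supported ACD appointments", and ACD2 is the second of these.

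The same section opens by saying that participants in both arms answer the pre-post questions on primary and secondary endpoints at T1 and T2.

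**Analysis and power.** Required sample size and power analysis gives about 150 participants for power above .8 on the condition-by-time interaction, "both regarding our primary and secondary endpoints". Statistical analyses adds that "analyses of proxy burden and of secondary endpoints will be based on Bayesian linear mixed effects models".

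**The concern.** A condition-by-time interaction compares the pre-post change in one arm with that in the other. If only one arm is assessed, there is nothing to compare. A change in congruence among treatment-arm proxies could reflect the intervention, the passage of time, repeated questioning, or the proxy having sat in on ACD2, where the person with dementia settles their decision. The T2 proxy answer is also collected only where a directive is present, a condition that arises after randomisation and is partly affected by treatment.

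At stake is whether the trial can say anything comparative about congruence. Because the gap lies in data collection, neither imputation nor a later analysis plan can fill it. Recruitment runs from March 2025 to January 2027, and control-arm answers not collected at a visit cannot be recovered.

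**Working it through.** **1. The stated power figure.** It comes from simulation, and the article gives no numeric effect size, variance components, pre-post correlation or error rate, so it cannot be strictly reproduced. A closed-form check under assumptions (standardised effect d = 0.5 for a moderate effect, two-sided 0.05, no loss, a proxy for every participant) shows whether it is plausible for an endpoint measured in both arms.

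Allocation 2:1 of 150 gives 150 × 2/3 = 100 and 150 × 1/3 = 50.

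Power = Φ( d / (s·√(1/n_T + 1/n_C)) − 1.96 ), with s = 1 for a post-only comparison and s = √(2(1 − ρ)) for a change score with pre-post correlation ρ. At ρ = 0.5, s is also 1.

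- 100:50, s = 1: √(0.01 + 0.02) = 0.173; 0.5/0.173 = 2.887; Φ(0.927) = 0.82.
- 75:75 (balanced groups of 150), s = 1: √(2/75) = 0.163; 0.5/0.163 = 3.062; Φ(1.102) = 0.865.
- Change score with ρ from 0.3 to 0.7: 0.68 to 0.96 at 100:50, and 0.74 to 0.98 at 75:75.

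So the general claim is plausible for endpoints timed at T1 and T2 in both arms.

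**2. Congruence on the Table 1 schedule.**

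| Listed occasion | Respondent | Treatment arm | Control arm |
|---|---|---|---|
| T1_Treatment | proxy | yes | none |
| ACD2 | person with dementia | yes | none |
| T2_Treatment | proxy | only if a directive is present | none |

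With n_C = 0 the term 1/n_C is undefined, so the power formula has no value. The model shows the same. Take the columns intercept, condition, time and condition × time. With treatment-arm rows only, condition equals 1 throughout, so it duplicates the intercept, and condition × time duplicates time. The rank is 2 of 4, against 4 of 4 with both arms. Neither the condition effect nor the interaction is estimable at any sample size or allocation ratio.

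**3. What is left within the treatment arm.** The power section expects about 50% to hold a directive at baseline and treats a rise of 20 to 30 points as relevant. If that rise is read as applying to directive presence (the sentence follows one on validity, so this is an assumption), 50 + 20 = 70% to 50 + 30 = 80% of treatment-arm participants seen at T2 would qualify for the T2 proxy questions. The other 20 to 30% would have no T2 value.

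**4. The conflicting text.** The opening of Data collection and the placement of footnote a suggest that the two items go to both arms. But Table 1 lists no time at which a control proxy answers them, and the only time listed for the person with dementia is an appointment that controls do not have.

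**The case against.** The strongest reply is that the two items are meant for both arms. The general statement on both arms precedes the treatment-arm questions, which are called additional. The Material text and footnote a restrict only the Statement. The shared Time cell may describe the Statement alone, and making T2_Treatment depend on a directive fits that. Fig. 2 and Additional file 1, which might settle the matter, are not at hand. This stands as far as intent is concerned: a reader might infer that no control will ever be asked, or that power is simply nil, and the documents do not establish that. They establish it for the listed schedule only. But on the favourable reading the two items have no listed time at all, so a correction is still needed.

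A reader might also call directive presence at T2 purely a result of treatment. That goes too far, since about half are expected to hold one at baseline. Nor is a single answer from the person with dementia a fault in itself; it can serve as the reference for two proxy ratings.

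Finally, the restriction may be deliberate. Asking control proxies about treatment preferences at T1 might prompt planning before directive presence, a primary endpoint, is recorded at T2. That is a fair reason to keep a treatment-only schedule, but then the analysis and power text must exclude congruence.

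**Conclusion.** The point holds as a conflict that must be resolved. On the only schedule given, congruence has no control-arm assessment, the condition-by-time interaction is not estimable (rank 2 of 4), and the power above .8 cannot apply to it. This conclusion rests on Table 1 and the definitions in Data collection. It does not depend on the 100:50 split, which may shift because the protocol allows the ratio to be adjusted, nor on the 70 to 80% illustration.

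The reach is limited. Congruence is one of three secondary endpoints and is not among the three main research questions. The primary endpoints and the other two secondary endpoints are timed in both arms and are untouched. A reader might infer that the sample size as a whole is undermined; the check in step 1 gives no support for that.

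**What to change.** Reconcile Table 1, Data collection, Material and the two statistical sections in one of two ways.

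**Option A: a two-arm endpoint.** Schedule the two congruence items in both arms, whether or not a directive exists, at least at T2 and with proxy and person with dementia asked separately. Keep the Statement of Treatment Preferences as a descriptive treatment-arm measure. With T2 only, the analysis is a randomised post-treatment comparison, and the text must say so in place of the interaction. Under the step 1 assumptions, power would be about 0.82 at 100:50, and lower with dropout or where no proxy takes part. Asking proxies at T1 as well adds a baseline; the text should then name which answer from the person with dementia is the reference. The cost is two items per respondent at visits both arms already attend, plus an amendment. T1 questioning carries a small risk of prompting planning in controls. Participants already past T2 cannot be recovered.

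**Option B: a descriptive measure.** If the treatment-only schedule is intended, declare congruence descriptive within the treatment arm, state that its T2 value depends on a directive being present, and remove it from the condition-by-time analysis and the power statement. The cost is wording only; the trial then makes no comparative claim about congruence.

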#### Recruitment

Recruitment will focus on patients or clients from the dementia care network in Siegen-Wittgenstein and will be further integrated within the locally operating DeCM (the dementia care managers will approach suitable patients in their work context). Recruitment will also extend to surrounding regions of Siegen-Wittgenstein to inform general practitioners, neurologists, pharmacies, associations, self-help groups, and the general public through local media channels. The network of participating practice partners represents the necessary care areas for DeCM and PwD (initial diagnosis, sector transitions, etc.) and includes an entire region with urban and rural areas. All partners have established care structures and prior experience in conducting and participating in scientific projects [14, 15], ensuring access to the target audience relevant to this trial. DeCM was already implemented in Siegen-Wittgenstein [16], and the dementia care managers already provide DeCM. They will invite patients or clients who meet the inclusion criteria. Based on our previous projects, recruitment in the hospital setting (geropsychiatry) will be supported by the physicians of the memory clinic located in the Klinikum Siegen.

#### Participant retention and withdrawal

To prevent selective drop-out due to cognitive impairments, several strategies will be applied to help participants attend their DeCM appointments. Upon agreement to participate, and if required, participants will receive reminder calls prior to the appointment. Missed appointments will be met with an offer to reschedule. If individuals decide to withdraw from participation, the reasons for dropping out of the study will be collected.

### Material

An overview of the instruments used for all measured variables is shown in Table 1. In addition to the existence of various advance health care documents (yes/no), the validity of an advance directive will be assessed, which is indicated by the existence of informed consent at the time the advance directive was created. For this purpose, a self-report questionnaire in accordance with the criteria for informed consent (adequate information, capacity to consent, voluntariness [17]) will be used.

**Table 1 Tab1:** Overview of collected constructs and applied instruments

Measured variable	Instrument	Time	Target individual
Primary endpoints			
Presence and validity of advance care documents	closed questions based on DECIDE-I study [9], usage of advance directive	T1, T2, T3-T7	PwD and proxy
Proxy burden	Zarit Burden Interview (7 items, [18–21]), Burden Scale for Family Caregivers (BSFC-s, 10 items, [22]).	T1, T2, T3-T7	proxy
Secondary endpoints			
Patient autonomy	Decisional Autonomy Scale (DAS, [23]), Perceived Autonomy in Old Age scale (WAA, [24, 25])	T1, T2	PwD
Patient-proxy congruence with treatment preferences	two items with different versions for PwD and proxy, Statement of Treatment Preferences^a^ [26]	$$\text {T1}_{Treatment}$$+$$\text {T2}_{Treatment}$$(proxy), ACD2 (PwD)	PwD and proxy separately
Decisional Conflict	Decisional Conflict Scale (16 items, [27])	T1, T2	PwD
Moderators, Mediators, confounding variables			
Demographic variables	diagnosis, age, gender, education, employment, living situation	T1, T3-T7	PwD
Health-related preferences	health literacy (single item, see [28]), need for autonomy (single item, see [29]	T1	PwD
Health-related variables	single screening item & checklist based on Mini-DIPS (Short Structured Clinical Interview for diagnosing Mental Disorders) [30]	T1	PwD
Depression	Geriatric Depression Scale [31]	T1	PwD
Cognitive status	Mini Mental Status Test [32]	T1	PwD
Advance Care Decision-Making^a^			
Value anamnesis	According to [11]	ACD1	PwD
Capacity to consent	CAT-AD [33]	ACD2	PwD
Advance care documents	Template by Bavarian State Ministry	ACD2	PwD and proxy

T1-T7 are illustrated in detail in Fig. 2

^a^Only for participants in treatment arm who create an advance directive

Patient-proxy congruence is used to evaluate how accurately the future proxy can assess the treatment preferences of the PwD. It will be assessed with two items developed for this purpose, both of which will be answered by the future proxy and by the PwD. For participants in the treatment arm who create an advance directive, the statement of treatment preferences will also be collected, for which three scenarios from [34] were adapted according to the target population. Details are found in Additional file 1. While the hypothetical scenarios will be presented directly to the proxy, PwD will be exposed indirectly – in the context of the advance directive process – to the scenarios in order to minimize burden for the individual.

The implementation of ACD is divided into the collection of the value anamnesis [11], the examination of the capacity to consent using the CAT-AD [33], and the optional creation of advance documents. The CAT-AD is an adaptation of the MacCAT-T [35, 36] and DCAT-PAD [37, 38]. It has already been applied and validated in the DECIDE project, achieving an interrater reliability of $$> 80\%$$ per item, while the agreement with the overall scale of capacity to consent was 100% [33]. While the CAT-AD is evaluated for study purposes as part of supervision and quality control, the value anamnesis and the advance documents will be left with the participants for personal use and will not be further used for study purposes.

To simplify the data collection process for the cognitively impaired target group, the rating scale was uniformly adapted to a 5-point Likert scale (“strongly disagree” to “strongly agree”) for the majority of the questionnaires and the wording of the questions was adapted accordingly. Lastly, DeCM will be assessed with a range of questions developed and evaluated in a past study focusing on the implementation of DeCM [16]. These assessments do not represent an endpoint in the present study and are not further described in this protocol (for more details, see [16]).

